### Population

Resistant hypertension is defined as casual blood pressure during clinical examination of more than 140/90 mmHg (in patients below 60 years of age or with diabetes mellitus) or more than 150/90 mmHg (in patients above 60 years of age) despite treatment with a multidrug combination consisting of a diuretic and an ACEI/ARB, a centrally acting drug, and an alpha blocker or calcium channel blocker [18]. All reference blood pressures will be taken as a mean of the 2nd and 3rd measurements during a single examination measured at least 3 min apart.

### Inclusion and exclusion criteria

#### Inclusion criteria

Both genders aged between 18 and 75 years and eligible for the study through screening confirming the presence of resistant hypertension as defined above.

#### Exclusion criteria

Patients with a systolic blood pressure value over 220 mmHg requiring immediate adjustments of therapyPatients with moderate to severe renal insufficiency (acute or chronic) with glomerular filtration rate of less than 30 ml/minPatients with active bronchospastic disordersHeart failure classes III and IVSevere bradycardia (heart rate below 50/min), 2nd and 3rd degree AV blockPregnant or lactating womenPatients with a history of hypersensitivity to any of the drugs under studyPatients already using beta blockers

#### Suspension criteria

Subject’s demand to discontinue the studySerious adverse events or unusual changes in clinical test resultsPrincipal investigator’s decision to terminate the study (low rates of compliance, complications, or unable to sustain the study for various reasons)

### Randomization

Randomization will be performed using computer-generated random number allocation tables generated by SPSS v16.0 software package (SPSS Inc., Chicago, IL, USA), based on a 1:1 allocation between groups. Patients will be assigned a recruitment number once they provide informed written consent. Each recruitment number will be subsequently allocated a computer-generated study number with a corresponding treatment kit number. These kit numbers will determine allocation to the treatment group or placebo group. The personnel administering the study medication will be blinded to the treatment group. Random number allocation tables and lists will be maintained in password-protected files accessible only in the event where unblinding is deemed necessary.

### Blinding

The study drugs are double blinded to both investigators and subjects. The drug manufacturing will be done by Astron Lanka (PVT) Ltd., Colombo, Sri Lanka, and they will be responsible for the labeling of the capsules with code numbers.

### Interventions

The treatment drug is a capsule containing propranolol 40 mg as the active ingredient. The placebo will be manufactured to have a similar appearance, shape, weight, taste and color as the propranolol 40-mg capsule. The subjects will receive either propranolol 40 mg or an identical placebo taken three times a day for a period of 3 months.

### Study groups

Treatment group: propranolol capsule and standard treatmentsControl group: placebo capsule and standard treatments

### Study period

The study will be conducted for a period of 3 months. The visits and the evaluations will be done as follows: screening (visit 0), 1 month (visit 1), 2 months (visit 2) and 3 months (visit 3).

### Outcomes

Primary outcomes: the primary outcomes of the study are to find a statistically significant difference between the fall in mean systolic and mean diastolic blood pressure measured by ABPM (ambulatory blood pressure monitoring) from baseline between the two groups.

Secondary outcomes:To determine the difference in cardiovascular outcomes, including acute coronary syndrome, acute stroke and acute heart failure, between groupsTo determine the variations in plasma and urinary electrolytes between the two groups at measured endpointsTo assess renal outcomes as measured by the glomerular filtration rate between groupsTo determine variations in plasma renin activity (PRA) and angiotensin:aldosterone ratios between the study groupsTo determine differences in oxidative stress between the study groups using nitric oxide as a surrogate markerTo assess safety outcomes, including the incidence of serious adverse effects, between the two groups at measured endpoints

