### Sample size

The sample size calculation was based on formulae for analysis between differences of means. The value for alpha was set at 0.05 and the value for 1 − beta was set at 0.9. Sample sizes were calculated for a difference of systolic blood pressure by 10 mmHg and diastolic blood pressure by 5 mmHg. Standard deviation values were taken as 18 mmHg for systolic blood pressure and 10.7 mmHg for diastolic blood pressure as per prior investigations on patients with resistant hypertension. Using the above parameters the calculated sample sizes were 140 and 180 patients to detect differences in systolic and diastolic blood pressures, respectively. Using the greater number and adjusting for dropout and noncompliance rates a sample of 200 patients will be recruited with a 1:1 allocation per group.

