#### Study schedule

The detailed items that will be measured at every visit are described in Fig. 2. During the screening visit, the following baseline examinations will be carried out. Pulse rate and blood pressure measurements in the office (a mean of the 2nd and 3rd measurements on a seated patient during a single examination, three blood pressure measurements will be taken at least 3 min apart from each other). During this screening visit patients will be evaluated for compliance and other factors for lack of control such as failure to adhere to lifestyle advices, poor blood pressure measurement technique and the use of medications that interfere with blood pressure. This will be followed by a run-in period of 4 to 8 weeks where patients identified as having resistant hypertension will be subjected to optimization of their existing drug regimen. The drug dosages will be adjusted to the maximum recommended dose or the maximum tolerated dose. After the run-in period patients will be enrolled into the study if they fulfill the inclusion and exclusion criteria. This will be the enrollment visit. In this visit serum urea, creatinine, sodium, potassium and PRA and aldosterone levels will be measured. Estimation of sodium and potassium excretion will also take place with a 24-h estimation of urinary electrolytes. Baseline oxidative stress will be assessed by estimation of nitric oxide levels. An electrocardiogram will be taken to assess cardiac rhythm. During this visit 24-h ABPM, using a monitor validated to the standards of the British Hypertension Society (BHS), will be undertaken. The mean daytime blood pressure will be calculated from values measured between 9:00 a.m. and 11:00 p.m., the mean night blood pressure from values measured between 1:00 a.m. and 6:00 a.m. The mean 24-h blood pressure will be calculated as the mean of all the measured values [19]. This will enable us to exclude patients with white coat hypertension.

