### Statistical analysis

Parametric and nonparametric statistical tests will be applied using the SPSS version 16 (SPSS Inc., Chicago, IL, USA) and Stata/SE 10.0 (StataCorp Inc., College Station, TX, USA) for data analysis. Descriptive data will be analyzed for linearity and will be expressed as percentages, median and mean. The two groups will be compared for uniformity on sociodemographic variables, clinical manifestations and laboratory parameters at baseline. After completion, primary and secondary outcomes will be compared in the groups using statistical methods for comparison of means and using regression analysis. For each of the outcomes, multilevel regression analysis will be used to examine differences between trial arms. For binary outcomes the model will be logistic and for continuous outcomes the model will be linear regression. All analyses will follow intention-to-treat principles and a prespecified analysis plan. Where appropriate, sensitivity analyses will be conducted (for example, control for additional covariates; and bootstrapped *p* values for skewed outcomes). In the case of missing data values, we will apply mean imputation and regression imputation where rates are low, and consider multiple imputations where they exceed 10%. A *p* value < 0.05 will be considered significant.

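### Two primary blood pressure outcomes at an unadjusted 0.05, with no either/both rule and no named ABPM average: depending on the rule, the design exceeds 5% familywise error or, at the planned 180 evaluable, falls short of 90% power

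*Protocol article*

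**What the plan says.** Under Outcomes, the protocol article names its primary outcomes in the plural: "the primary outcomes of the study are to find a statistically significant difference between the fall in mean systolic and mean diastolic blood pressure". The readings come from ABPM and are compared between the groups. The Abstract says the same. Neither place says whether success needs one pressure or both.

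Under Statistical analysis there is one threshold for everything: a p "value < 0.05 will be considered significant". No adjustment is mentioned. The same section refers to a prespecified analysis plan, which is not shown.

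Under Sample size, "The value for alpha was set at 0.05 and the value for 1 − beta was set at 0.9". Then "Sample sizes were calculated for a difference of systolic blood pressure by 10 mmHg and diastolic blood pressure by 5 mmHg", and "Standard deviation values were taken as 18 mmHg for systolic blood pressure and 10.7 mmHg for diastolic blood pressure". The result is that "the calculated sample sizes were 140 and 180 patients to detect differences in systolic and diastolic blood pressures, respectively". The larger figure is raised to 200 to allow for dropout and noncompliance; no rate is given.

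Under Study schedule, three ABPM averages are defined: daytime, night and 24-h ("The mean 24-h blood pressure will be calculated as the mean of all the measured values"). They appear in the account of the enrollment visit, next to the exclusion of white coat hypertension. Outcomes does not say which of them is the primary measure.

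**The concern.** With two primary outcomes, the error rate and the power of the trial's main claim depend on the rule that joins them. If a significant result on either pressure makes the trial positive, two tests at 0.05 give more than a 5% chance of a false positive. If both must be significant, no adjustment is needed, but the chance of success is lower than the power of either test alone. The 90% under Sample size belongs to each pressure separately, so it is not the power of a both-required claim.

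The unnamed ABPM average adds a choice. Three averages of the same recording are available, and the article does not tie the primary outcome to one of them. The standard deviations under Sample size come from prior investigations with no averaging window stated, so they do not settle it either. If these choices are made after the data are seen, the stated 5% and 90% no longer describe the trial.

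**Working it through.** **Inputs.** From Sample size: alpha 0.05, power 0.90, differences of 10 and 5 mmHg, SDs of 18 and 10.7 mmHg, totals of 140 and 180, 200 recruited 1:1. Assumed: two-sided tests (sidedness is not stated), and a systolic-diastolic correlation ρ from 0 to 0.9 (not in the document). If 180 is the number left after dropout, the implied loss is 1 − 180/200 = 10%.

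**Step 1: reproduce the stated sample sizes.** Per arm, n = 2 (1.960 + 1.282)² (SD/difference)², with (1.960 + 1.282)² ≈ 10.51.
- Systolic: 2 × 10.51 × (18/10)² = 68.1, so 69 per arm and 138 in total. The t-test version gives 69.06, so 70 per arm and 140. The stated 140 is reproduced.
- Diastolic: 2 × 10.51 × (10.7/5)² = 96.3, so 97 per arm and 194 in total (196 with the t-test). The stated 180 is not reproduced. One-sided 90% gives 158, two-sided 80% gives 144 and one-sided 80% gives 114, so none of these variants explains it.

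**Step 2: power of each test alone.** Power = Φ(difference / (SD √(2/n)) − 1.960).
- 90 per arm: systolic Φ(3.727 − 1.960) = 96.1%; diastolic Φ(3.135 − 1.960) = 88.0%.
- 100 per arm: systolic 97.5%; diastolic 91.1%.

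**Step 3: the two possible rules.** The two test statistics are treated as bivariate normal with correlation ρ. At ρ = 0, familywise error if either suffices is 1 − 0.95² = 9.75%. Joint power if both are required, at 180 evaluable, is 0.9614 × 0.8799 = 84.6%.

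| Assumed ρ | Either suffices: familywise error | Either suffices: power at 180 | Both required: power at 180 | Both required: power at 200 |
|---|---|---|---|---|
| 0 | 9.75% | 99.5% | 84.6% | 88.8% |
| 0.5 | 9.1% | 98.2% | 85.9% | 89.6% |
| 0.7 | 8.4% | 97.4% | 86.7% | 90.2% |
| 0.8 | 7.8% | 96.9% | 87.2% | 90.5% |
| 0.9 | 7.0% | 96.4% | 87.7% | 90.9% |

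If both are required, the error rate for the joint claim is at most 5% without adjustment.

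**Step 4: where the power shortfall comes from.** At 180 evaluable, diastolic power alone is 88.0%, which is 2.0 points below 90% before any joint rule applies. Requiring both takes a further 0.3 points (ρ = 0.9) to 3.4 points (ρ = 0). Correcting the count to 194 would not remove the second part: at ρ = 0, joint power would be 0.9719 × 0.9022 = 87.7%. Joint power of 90% needs about 208 evaluable patients at ρ = 0, 204 at 0.5, 200 at 0.7 and 198 at 0.8.

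**The case against.** The strongest reply is that the analysis plan, which the article mentions and which is not shown, may hold the rule and name the average. That is fair, and it limits the point to what the article itself fixes: two primary outcomes, an unadjusted 0.05 and a sample size for each pressure separately. Those statements need reconciling whatever the plan says. If the plan requires both, the 90% has to be restated; if it lets either suffice without adjustment, 5% does not hold.

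A second reply is that joining systolic and diastolic with *and*, and sizing to the larger number, suggests that both are required. On that reading 0.05 for each is correct. The wording allows this but does not say it, and the only consequence would then be on power. With all 200 evaluable, joint power is 88.8% to 90.9%, close to target. However, the article expects dropout, so 200 is the favorable end.

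A third reply is that much of the power gap is an error in the diastolic count and has nothing to do with the decision rule. This stands in part, as Step 4 shows.

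Two stronger readings are tempting and are not supported. A reader might infer that the trial controls neither error nor power. The two failures belong to alternative rules: when either pressure suffices, power is above 96%, and when both are required, error is within 5%. A reader might also count two pressures by three averages as six primary tests and quote an error rate for the best of six. The article defines the averages at enrollment and nowhere says that all are tested as primary. The missing name is an ambiguity to resolve; it is not a stated plan for six tests.

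**Conclusion.** The point holds in conditional form. The article fixes two primary outcomes at an unadjusted 0.05 and powers each separately, without the rule that joins them and without naming the primary ABPM average. If either suffices, familywise error is about 7.0% to 9.75%, with power above 90%. If both are required, error is at most 5% and joint power is 84.6% to 87.7% at 180 evaluable, or 88.8% to 90.9% at 200, against the stated 90%. Two of the percentage points lost at 180 come from a diastolic sample size that does not follow from its own inputs.

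These figures assume two-sided tests, the protocol's own differences and SDs, and ρ between 0 and 0.9. The unseen analysis plan could already settle the rule. The article's sample size statement would still need to say which claim its power serves.

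**What to change.** Name one ABPM average as primary, for example the change in the 24-h mean at 3 months, and make the other averages secondary. Test systolic first at two-sided 0.05, and test diastolic at 0.05 only if systolic is significant. This holds familywise error at 5% with no loss of alpha, and systolic has about 96% power at 180 evaluable.

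Correct the diastolic count to about 194 or restate its power. Under the fixed sequence, a diastolic claim needs both tests to succeed, so its power is the joint figure above: about 85% to 88% at 180.

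The cost is two or three sentences, and Trial status says that enrollment has not started. The downside is that diastolic cannot be claimed if systolic fails.

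Declaring both required at 0.05 each, with the joint power restated, is equally valid. Splitting alpha at 0.025 each would also control error, but it lowers diastolic power at 180 to about 81%.

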### Procedures

#### Recruitment

Participants will be recruited from the outpatient medical clinics of the National Hospital of Sri Lanka, Colombo, Sri Lanka.

#### Study schedule

The detailed items that will be measured at every visit are described in Fig. 2. During the screening visit, the following baseline examinations will be carried out. Pulse rate and blood pressure measurements in the office (a mean of the 2nd and 3rd measurements on a seated patient during a single examination, three blood pressure measurements will be taken at least 3 min apart from each other). During this screening visit patients will be evaluated for compliance and other factors for lack of control such as failure to adhere to lifestyle advices, poor blood pressure measurement technique and the use of medications that interfere with blood pressure. This will be followed by a run-in period of 4 to 8 weeks where patients identified as having resistant hypertension will be subjected to optimization of their existing drug regimen. The drug dosages will be adjusted to the maximum recommended dose or the maximum tolerated dose. After the run-in period patients will be enrolled into the study if they fulfill the inclusion and exclusion criteria. This will be the enrollment visit. In this visit serum urea, creatinine, sodium, potassium and PRA and aldosterone levels will be measured. Estimation of sodium and potassium excretion will also take place with a 24-h estimation of urinary electrolytes. Baseline oxidative stress will be assessed by estimation of nitric oxide levels. An electrocardiogram will be taken to assess cardiac rhythm. During this visit 24-h ABPM, using a monitor validated to the standards of the British Hypertension Society (BHS), will be undertaken. The mean daytime blood pressure will be calculated from values measured between 9:00 a.m. and 11:00 p.m., the mean night blood pressure from values measured between 1:00 a.m. and 6:00 a.m. The mean 24-h blood pressure will be calculated as the mean of all the measured values [19]. This will enable us to exclude patients with white coat hypertension.

After randomization patients will enter the clinical trial and will be given either propranolol 40 mg three times a day or a placebo which will be added to the patients’ routine medication. At the first two follow-up visits (visits 1 and 2) the following examinations and investigations will be performed: pulse rate and blood pressure measurements (as detailed above), measurements of serum sodium, potassium, urea and creatinine levels and an electrocardiogram. During the follow-up visits, if blood pressure is not controlled both drug and placebo dose will be doubled once (maximum dose of propranolol used in this study will be 80 mg three times daily). Three months after initiation of the drug, final examination of the patients will be carried out (visit 3), as described in Fig. 2.

### Measurement tools

#### Anthropometric measurements

Body weight will be measured using a calibrated electronic floor scale (SECA 815 by SECA GmbH & Co. Kg., Hamburg, Germany) to the nearest 0.1 kg. Height will be measured to the nearest 0.1 cm using an upright plastic portable Stadiometer (SECA 217 by SECA GmbH & Co. Kg., Hamburg, Germany). Body Mass Index (BMI) will be calculated as weight (in kilograms) divided by the square of height (in meters). Waist circumference (WC) will be measured with a nonelastic tape (SECA 203 by SECA GmbH & Co. Kg., Hamburg, Germany) at a point midway between the lower border of the rib cage and the iliac crest at the end of normal expiration. Similarly, hip circumference also will be measured at the widest part of the buttocks at the intertrochanteric level to the nearest 0.1 cm. All anthropometric measurements will be made by using standard equipment and following World Health Organization (WHO) guidelines.

#### Compliance calculation

Subjects will be asked to return any remaining drugs and their compliance will be evaluated by using the formula given below:$$ C o m p l i a n c e\kern0.2em \left(\%\right)=\left[\frac{\left( Distributed\kern0.2em  drugs{\textstyle \mathit{\hbox{-}}} remaining\kern0.2em  drugs\right)}{Distributed\kern0.2em  drugs}\right]\times 100 $$

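### The compliance formula divides by capsules distributed rather than capsules due, so it equals adherence only when supply exactly matches the doses due by the return date

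*Protocol article*

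**What the plan says.** The Compliance calculation section bases compliance on returned study drug: "Subjects will be asked to return any remaining drugs and their compliance will be evaluated by using the formula given below". The formula divides distributed minus remaining by distributed and multiplies by 100. The prescribed regimen and the time between dispensing and return do not appear in it.

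The Interventions section gives the scheduled intake: "The subjects will receive either propranolol 40 mg or an identical placebo taken three times a day for a period of 3 months". It describes one capsule strength: "The treatment drug is a capsule containing propranolol 40 mg as the active ingredient". The Study period section places follow-up visits at 1, 2 and 3 months. The Study schedule section adds that during follow-up "if blood pressure is not controlled both drug and placebo dose will be doubled once".

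Compliance has one stated use. The Suspension criteria section lists "low rates of compliance, complications, or unable to sustain the study" among the grounds on which the principal investigator may decide to terminate, without a threshold. The Statistical analysis section specifies intention to treat and describes no compliance-based population or analysis.

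**The concern.** Adherence is the share of prescribed doses that were taken, so its denominator should be the number of doses prescribed over the interval. The printed denominator is the number handed out. The two agree only if each patient receives exactly the capsules due and returns on exactly the day they run out. Three intakes a day and visits at calendar months make this unlikely to hold for every patient, and the number due can also change if the dose is doubled.

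This is a rule that the article states, not a detail left to a fuller document. At stake are the adherence figure that will be reported beside the efficacy result and the information available to an investigator judging whether compliance is low. A figure that moves with pack size and visit date serves neither purpose well.

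**Working it through.** The article gives no compliance percentage to reproduce, so the check evaluates the formula itself.

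**Notation.** D = capsules distributed, R = capsules returned, E = capsules due between dispensing and return.

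- Article's formula: 100 × (D − R)/D
- Formula based on doses due: 100 × (D − R)/E

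**Inputs from the article.** Three intakes a day (Interventions) and visits about a month apart (Study period).

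**Assumptions.** One capsule per intake before any doubling, so E = 3 × days. D and the actual visit day are not given and are varied below.

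**1. Fully adherent patient who returns all the surplus.** Here D − R = E, so the article's score is 100 × E/D and the score based on doses due is 100%.

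| Assumed situation | E | D | Article's score |
|---|---|---|---|
| Exact supply, day 30 | 90 | 90 | 100% |
| 90 issued, return on day 28 | 84 | 90 | 93.3% |
| 90 issued, return on day 26 | 78 | 90 | 86.7% |
| 10% surplus, day 30 | 90 | 99 | 90.9% |
| 20% surplus, day 30 | 90 | 108 | 83.3% |

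Over 90 days with E = 270 the percentages for a given surplus are the same: 270/297 = 90.9% and 270/324 = 83.3%.

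**2. Late visit.** With 90 issued and a return on day 35, E = 105. A patient who has none left scores (90 − 0)/90 = 100%. At most 90/105 = 85.7% of the doses due can have been taken.

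**3. Upper limit.** R cannot be negative, so the article's score cannot exceed 100% for any D. Taking more than prescribed cannot show.

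**4. Dose doubling.** If doubling means two 40 mg capsules per intake (an assumption; no other strength is described), 180 rather than 90 are due in 30 days. If supply follows the regimen visit by visit, D changes with E and no new error arises. If it does not, the formula has no term to correct for it. As an extreme case, a patient issued 180 with 90 due who takes all 90 scores (180 − 90)/180 = 50%.

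**5. Patient who brings nothing back.** The article's score is always (D − 0)/D = 100%, even for a patient who took 45 of 90 and discarded the rest. With doses due as the denominator the score is D/E: 100% at no surplus, 99/90 = 110% at a 10% surplus and 108/90 = 120% at a 20% surplus. The changed denominator does not remove this problem. It only makes an implausible value visible when a surplus was issued.

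**The case against.** The strongest reply is that the article gives no dispensed quantity and no visit window, and a journal article may leave both to the full protocol. If supply equals doses due, the two formulas are identical, and a 90-capsule pack returned on day 30 scores a perfect taker at 100%. This stands against any claim about the size of the error. A reader might infer that adherent patients will score well below 100%. The article does not show that: the low values come from assumed surpluses and early visits. The reply does not rescue the formula, which is correct only in the special case of an exact match, and the article does nothing to secure that match.

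A reader might also blame the denominator for the 100% given to a patient who returns nothing. Step 5 shows otherwise. The cause is that every capsule not returned counts as taken, which limits any pill count.

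A third objection concerns coding compliance as unknown when nothing comes back. The article asks only for leftover drug, so with an exact supply a perfect taker has nothing to return and would be coded unknown. This is right, and the rule works only if empty containers must be returned too.

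Finally, "low rates of compliance" is a matter for investigator judgement. The criterion has no threshold and does not cite the formula, so no suspension follows mechanically from a biased score. It would also be too strong to infer that a null result could not be separated from poor adherence. Pulse rate is recorded at follow-up and gives some independent indication of beta-blocker exposure. Both limits on the consequence stand.

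**Conclusion.** The concern holds in a limited form. The formula measures the share of supply not returned, and it is adherence only when the number distributed equals the number due at return. It understates adherence after a surplus or an early visit, can overstate it after a late visit, and cannot exceed 100%.

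Under the assumed supplies and visit days, a perfect taker scores between 83% and 93%, and the late-visit example scores 100% when coverage is at most 85.7%. These figures illustrate the mechanism and are not estimates for this trial. The counting of lost or discarded capsules as taken is a separate limitation.

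The point is minor. No stated estimate, test or analysis population depends on compliance, and the intention-to-treat comparison is unchanged. The gain is an accurate adherence figure for interpreting the result and better information for a judgement of low compliance.

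**What to change.** Replace the formula, computed separately for each visit interval, with:

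Compliance (%) = (dispensed − returned) / (capsules due between dispensing and return under the regimen then assigned) × 100.

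Ask patients to return all containers, including empty ones, and code compliance for that interval as unknown when containers are not returned. Use this figure for reported adherence and when judging low compliance under the Suspension criteria. Values above 100% should be shown rather than truncated, since they indicate either extra intake or lost capsules. Capsules discarded from a returned container will still count as taken, and the report should say so.

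The cost is small. The existing formula already needs the dispensed and returned counts, so only the dispensing and return dates and the assigned regimen must be linked to them. Some compliance values will be missing that the present formula would have scored as 100%. Where supply equals doses due, the new formula gives the same value as the old one. The Trial status section says enrollment has not started, so the change can be made before any counts are collected.
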